**Results are rounded up to the nearest integer**

**Results from OpenEpi, Version 3, open source calculator –SSC cohort.**

Considering drop-outs, a total of up-to 75 (but more than 60) subjects in total will be considered.

Study Population:

COVID-19 positive subjects.

# Subject Eligibility:

(a) Inclusion Criteria

1. Age > 18 years
2. All sexes
3. Case definitions for inclusion in the study will include mild to moderately severe cases as defined in the Guidance on appropriate treatment of suspect/confirmed case of COVI19 issued by Ministry of Health and Family Welfare, Govt of India on 07 Apr 2020.
   Mild: Cases presenting with fever and/or upper respiratory tract illness (Influenza like Illness, ILI); Moderate: Pneumonia with no signs of severe disease (Respiratory Rate 15 to 30/minute, SpO2 90%-94%). OR
4. Laboratory confirmed SARS CoV-2 infection within last 10 days or SARS CoV-2 test result pending with a high clinical suspicion as defined by: Cough of more than 10 days duration OR
5. Bilateral pulmonary infiltrates on chest X Ray / CT scan or new hypoxaemia defined as SpO2 <94% on room air, where no alternative explanation for respiratory symptoms can be given

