# Symptomatology and Pathophysiology of the disease:

Below table gives an overview of classification of COVID 19 patients:

| TYPE | PRESENTATION |
| --- | --- |
| Asymptomatic | COVID nucleic acid test positive. Without any clinical symptoms and signs and the chest imaging is normal |
| Mild | Symptoms of acute upper respiratory tract infection (fever, fatigue, myalgia, cough, sore throat, runny nose, sneezing) or digestive symptoms (nausea, vomiting, abdominal pain, diarrhea) |
| Moderate | Pneumonia (frequent fever, cough) with no obvious hypoxemia, chest CT with lesions. |
| Severe | Pneumonia with hypoxemia (SpO2 < 92%) |
| Critical | Acute respiratory distress syndrome (ARDS), may have shock, encephalopathy, myocardial injury, heart failure, coagulation dysfunction and acute kidney injury. |

Coronaviruses are enveloped, positive-sense, single-stranded RNA viruses of ~30 kb. They infect a wide variety of host species^[[8]](#endnote-8)^. They are largely divided into four genera; α, β, γ, and δ based on their genomic structure. α and β coronaviruses infect only mammals^[[9]](#endnote-9)^. Human coronaviruses such as 229E and NL63 are responsible for common cold and croup and belong to α coronavirus. In contrast, SARS-CoV, Middle East respiratory syndrome coronavirus (MERS-CoV) and SARS-CoV-2 are classified to β coronaviruses.

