# Study Design

Overview of the Study Design

- This is a randomized, 2-arm, parallel group, double-blind, 1:1 ratio, controlled, exploratory trial with a study period of 30 days from the of enrolment.
- A total of up-to 75 known COVID-19 positive (with positive RT-PCR) patients will be enrolled in the study.
- All the patients enrolled in the study will get the Investigational Product (IP-1 and IP-2), or 2 capsule of Placebo in similar sized and colored bottles, two times daily for the 1^st^ 15 days. From 16^th^ day onwards patients will get one capsule twice daily i.e. IP-2 or capsule placebo up to day 30.
- Patients will undergo laboratory investigations upon enrolment and on last visit. RTPCR for COVID will be done on day 5 (+ 1 day).
- Patients and doctors treating will not be knowing what the participating subject has received. Subjects will be given coded bottles, containing dose for 30 days.
- No medicine which his/her physician is giving will be stopped. No modifications shall be suggested in their diet and daily routine physical activities.
- Thus, patients enrolled in the study will get the IP / Placebo in addition to the standard of care which they were already receiving at the time of enrolment.
- Half of patients will be getting Cap. IP and half will be getting Cap. Placebo throughout the study duration of 1 month.

Study period for enrolled patients will be 30 days:

- Enrollment (day 0): After Informed Consent Process, Demographics and other information for CRF will be recorded. Investigations: COVID 19 RTPCR, Lymphocyte subset analysis (TH1, TH2, Th17, IL6, NK Cells and CD markers); Immunoglobulin IGG (Serum); Immunoglobulin IGM (Serum); Liver Function Test and Kidney Function Test will be done. Cap. bottle will be given to the patients with the dose lasting for 30 days.
- Day 3±1: COVID-19 RT PCR (quantitative) test will also be conducted on day 3 (±1) on 5 subjects of each group
- Follow-up 1: Day (5±1): COVID-19 RT PCR (quantitative) test will be conducted for all subjects on Day (5±1). CRF will be filled for knowing the overall status.
- Follow up 2 (15^th^ day+ 2 days): This follow up will be clinical/telephonic. CRF will be filled for knowing the overall status.

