## (b) Exclusion Criteria

1. Pregnant or lactating women
2. Symptoms of acute respiratory tract infection for more than seven days
3. More than 48 hours have elapsed between meeting inclusion criteria and enrolment
4. Subject is also a participant of any other clinical trial
5. Serious / long-standing co-morbid conditions

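### The inclusion criteria, joined by OR, do not require the positive RT-PCR that the design section promises, and they clash with the seven-day exclusion and the stated severity range

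*Protocol*

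**What the plan says.** Three places in the protocol describe a wholly COVID-19-positive population. Study Design states: "A total of up-to 75 known COVID-19 positive (with positive RT-PCR) patients will be enrolled in the study". Methods and Procedures asks for recently diagnosed COVID-19-positive patients, and its Study Population line says the same.

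The inclusion criteria (Subject Eligibility, part a) read differently:

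- **Item 3** gives mild and moderate case definitions, taken from national guidance on suspect or confirmed cases. It ends: "Moderate: Pneumonia with no signs of severe disease (Respiratory Rate 15 to 30/minute, SpO2 90%-94%). OR"
- **Item 4** accepts laboratory confirmation within the last 10 days, or a "SARS CoV-2 test result pending with a high clinical suspicion as defined by: Cough of more than 10 days duration OR"
- **Item 5** accepts "Bilateral pulmonary infiltrates on chest X Ray / CT scan or new hypoxaemia defined as SpO2 <94% on room air", provided that nothing else explains the respiratory symptoms.

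The exclusion criteria remove patients with "Symptoms of acute respiratory tract infection for more than seven days" and those for whom "More than 48 hours have elapsed between meeting inclusion criteria and enrolment". The classification table under Symptomatology and Pathophysiology describes severe disease as "Pneumonia with hypoxemia (SpO2 < 92" per cent).

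The Primary Outcome, listed within the Adverse Events text, is viral-load decline at 5 days together with early recovery. Data Analysis says that all collected data will be analysed under intention to treat.

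**The concern.** The eligibility list is what a site applies when it enrols. If it can be met without a positive test, the trial can randomise people who never had the infection. The primary outcome includes a fall in viral load by day 5, and a patient with no virus at day 0 cannot show one in either arm. Depending on how the outcome is coded, such a patient is a non-event in both arms or counts as cleared in both arms. Either way the difference between arms shrinks, and a trial of 60 to 75 patients has little power to spare.

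The criteria also disagree among themselves on symptom duration and on severity, so two people screening the same patient could reach different decisions.

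**Working it through.** **1. Which routes need a positive test?** The printed text allows more than one reading, so each is tried.

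| Reading | Routes without a positive test |
| --- | --- |
| Items 3, 4 and 5 are alternatives, as the printed OR says | Item 3 on clinical picture; item 5 on infiltrates or on hypoxaemia, with no other explanation |
| Item 5 completes item 4's definition of high clinical suspicion | Item 3 (its own closing OR is unaffected); pending test plus infiltrates or hypoxaemia |
| As above, and item 3 is also treated as required, against its printed OR | Pending test plus infiltrates or hypoxaemia |

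No reading makes a positive test necessary.

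**2. The cough route.** Item 4 needs cough for more than 10 days. The protocol's classification table lists cough among the symptoms of acute upper respiratory infection, and such symptoms beyond seven days are excluded. More than 10 days implies more than seven, so this route admits nobody. Unconfirmed patients enter through item 3 or item 5.

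**3. Oxygen saturation.**

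| SpO2 | Item 3 | Item 5 | Classification table |
| --- | --- | --- | --- |
| 92-93% | moderate | admitted | not in the severe band |
| 90-91% | moderate | admitted | severe |
| below 90% | outside the range | admitted | severe |

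No exclusion criterion removes severe acute disease.

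**4. The plan's own sample size.** Inputs from the sample-size table: 5% versus 35%, two-sided 5% level, 80% power, ratio 1:1. Mean proportion 0.20.

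- Kelsey: (1.960 + 0.842)² × 2 × 0.20 × 0.80 / 0.30² = 27.9, so 28 per arm and 56 in total.
- Fleiss, without continuity correction: [1.960 × √(2 × 0.20 × 0.80) + 0.842 × √(0.05 × 0.95 + 0.35 × 0.65)]² / 0.30² = 26.7, so 27 per arm and 54 in total.

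Both match the protocol, and the figure is not in dispute.

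**5. Illustration of dilution.** Two inputs are assumptions:

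- The share f without virus at baseline is set at 10, 20 and 30%. The documents give no figure.
- The 5% and 35% are taken as the day-5 outcome rates among infected patients. The sample-size table does not name its outcome.

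If such patients are non-events, each rate p becomes (1 − f)p. If they count as cleared, it becomes (1 − f)p + f. Power is that of the two-sided Fisher exact test at 28 per arm, summed over all possible outcomes.

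| f | Non-event: rates | Power | Cleared: rates | Power |
| --- | --- | --- | --- | --- |
| 0 | 5% vs 35% | 74% | 5% vs 35% | 74% |
| 10% | 4.5% vs 31.5% | 66% | 14.5% vs 41.5% | 52% |
| 20% | 4% vs 28% | 56% | 24% vs 48% | 37% |
| 30% | 3.5% vs 24.5% | 45% | 33.5% vs 54.5% | 25% |

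**6. Analysing only patients with detectable virus on day 0.** For a continuous outcome, take a standardised difference of 0.736. This is not in the protocol; it is the value that gives a two-sample t test 80% power at 30 per arm.

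| f | All patients: effect 0.736 × (1 − f), 30 per arm, SD unchanged | Detectable virus only: effect 0.736, 30 × (1 − f) per arm |
| --- | --- | --- |
| 10% | 71% | 76% (27 per arm) |
| 20% | 61% | 70% (24 per arm) |
| 30% | 50% | 64% (21 per arm) |

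Restriction recovers part of the loss, not all of it.

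**The case against.** The strongest reply is that the intent is clear. Three passages say COVID-19 positive, everyone has an RT-PCR on day 0, and a site would probably enrol only positive patients. Item 5 is not a bare oxygen reading, because it requires that nothing else explains the symptoms, and it may only complete item 4. The classification table is background, while item 3 is the operative definition. Handling of patients negative on day 0 may be left to an analysis plan that is not at hand. The trial is exploratory, blinded and randomised, so ineligible patients fall on both arms alike.

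Much of this limits the point without removing it. Intent stated elsewhere does not repair an eligibility list that omits the requirement, and step 1 shows that the milder readings still admit untested patients. An analysis plan cannot change who is enrolled.

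Four stronger inferences are not supported:

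- **That the cough route lets in unconfirmed patients.** The seven-day exclusion empties it.
- **That the 10-day confirmation limit contradicts the 48-hour exclusion.** They collide only if the positive test alone starts the 48-hour clock. A patient confirmed nine days ago who first meets the severity definition today satisfies both. The 10-day limit also does not by itself contradict the seven-day rule, since one counts from the test and the other from symptoms.
- **That the result would be biased in favour of the product.** The expected effect is dilution, in both arms.
- **That the loss of power is known.** It depends on an assumed share, an assumed outcome and an unstated counting rule. Early recovery, the other part of the primary outcome, is not covered by the viral-load argument.

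**Conclusion.** The point holds as an internal contradiction in eligibility. The inclusion criteria do not carry the positive RT-PCR that Study Design describes, and on any reading some patients can enter without it. One route into item 4 is void because an exclusion cancels it. Item 5 has no lower SpO2 limit, although item 3 confines entry to mild to moderate disease and gives 90-94% for moderate. Saturations of 90-91% are moderate in one section and severe in another; that last mismatch is minor and has no bearing on viral load.

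The consequence for the primary outcome is dilution of unknown size. On the assumptions in step 5, power falls from 74% to between 66% and 45% under the milder counting rule, and to between 52% and 25% under the harsher one. These figures show direction and sensitivity. They are not an estimate for this trial.

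**What to change.** Amend the eligibility text:

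1. Make the positive RT-PCR already stated in Study Design a mandatory criterion, joined by AND to the severity definition. The test-pending alternative then falls away.
2. Reconcile the cough-duration wording with the seven-day symptom exclusion.
3. Reconcile the SpO2 statements in item 3, item 5 and the classification table. Which threshold is right is for the sponsor and the investigator; this review does not choose one.
4. State which event starts the 48-hour clock.

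Optionally, analyse viral load in randomised patients with detectable virus in the pre-dose day-0 sample, alongside the full intention-to-treat analysis. A confirmation up to 10 days old does not guarantee virus on day 0, so this adds something beyond item 1. The set is defined by a pre-treatment property, which protects the comparison, and it uses a test already scheduled.

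The cost is a protocol amendment and possibly slower recruitment, for which the documents give no figure. The optional set is smaller: without extra enrolment, its t-test power is about 76, 70 and 64% at assumed shares of 10, 20 and 30%.

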## (b) Exclusion Criteria

1. Pregnant or lactating women
2. Symptoms of acute respiratory tract infection for more than seven days
3. More than 48 hours have elapsed between meeting inclusion criteria and enrolment
4. Subject is also a participant of any other clinical trial
5. Serious / long-standing co-morbid conditions

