# Randomization Process:

An alphanumeric coded set of IP/Placebo containers will be used. Participants will be automatically randomized to two groups in the ratio 1:1. Blind will be broken after the last follow-up of last enrolled subject is over.

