- Efficacy of the herbal extracts in COVID 19 positive patients (in declining viral load: time-point: 5 days and early recovery)

Secondary Outcomes:

- - Efficacy of the herbal extracts as an immune-modulator - TH1, TH2, Th17, IL6, NK Cells and CD markers; Immunoglobulin IGG (Serum); Immunoglobulin IGM (Serum): at 30 days.
  - Efficacy of the investigational product in reducing sequela of the disease
  - Safety analysis (Liver Function Test and Kidney Function Test) including serious allergic reaction of: rash, itching/swelling, severe dizziness, trouble breathing.

1. Details about the Investigator*

Name

Address

Telephone number

Profession (specialty)

Date of reporting the event to Ethics Committee:

Signature of the Investigator

Information marked ‘*’ must be provided.

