# Data Analysis

Overall blinding will be broken at 30 days i.e.at the end of the study. Depending upon ADRs / SAEs, individual blinding might be broken on case-to-case basis.

Paired t test and any other appropriate test will be applied for analysis.

As this is intent-to-treat design, all the data, even the dropped-out patients’ and lost to follow-up patient’s collected data will be analyzed.

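### The only analysis named for day-5 viral load is a paired t test; a between-arm model adjusted for day-0 viral load and days since symptom onset would be better and costs little

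*Protocol*

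**What the plan says.** - **Entry.** Protocol, Exclusion Criteria, item 2 excludes "Symptoms of acute respiratory tract infection for more than seven days". No lower limit is given.
- **A second timing rule.** Inclusion item 4 admits "Laboratory confirmed SARS CoV-2 infection within last 10 days or SARS CoV-2 test result pending with a high clinical suspicion", and defines that suspicion by "Cough of more than 10 days duration OR" (the final word links to the next item).
- **Outcome.** The Primary Outcome list, placed inside the Study Treatment section, describes efficacy as "in declining viral load: time-point: 5 days and early recovery". This point concerns only the viral-load part.
- **Measurements.** Study Design schedules RT-PCR at enrolment and a quantitative RT-PCR for all subjects at day 5. The Study Assessment Table puts the mark for quantitative RT-PCR at both visits.
- **Allocation.** Randomization Process: "Participants will be automatically randomized to two groups in the ratio 1:1". No stratification factor is named.
- **Analysis.** Data Analysis: "Paired t test and any other appropriate test will be applied for analysis". Methods and Procedures also justifies the sample size by reference to a paired t test. No covariate is named anywhere.

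**The concern.** Viral load in an acute infection can be expected to rise and then fall. Two patients with the same day-0 value can be on opposite sides of the peak, one about to climb and one already clearing, and their expected day-5 values then differ. Day-0 viral load alone does not separate them; days since onset carries further information. It is also distinct from severity, since a mild or a moderate case can be early or late.

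The named test uses none of this. A paired t test asks whether viral load changed within a group, and natural clearance alone can answer yes. The protocol describes no pairing of patients across arms. With about 30 to 37 patients per arm, what is at stake is precision, and how far the single observed result can be trusted if the arms happen to differ in stage.

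**Working it through.** **1. The protocol's own sample size.** Inputs from its table: 5% against 35%, 80% power, two-sided 5%, ratio 1.
- Kelsey: (1.960 + 0.842)² × 2 × 0.20 × 0.80 / 0.30² = 27.9, so 28 per arm, 56 in total.
- Fleiss without continuity correction: 27 per arm, 54 in total.

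Both agree with the table. They rest on a binary outcome, so they say nothing about the variance of viral load or what a covariate would explain.

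**2. What the named test does when the drug does nothing.** Paired t test in one arm of 30, with natural decline expressed in SDs of the change (assumed values):

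| Natural decline | Chance of p < 0.05 |
|---|---|
| 0.3 SD | 36% |
| 0.5 SD | 75% |
| 0.8 SD | 99% |
| 1.0 SD | above 99.9% |

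A significant within-arm result is therefore not evidence of a drug effect.

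**3. How far the arms may differ in stage.** Assumption: entry uniform over 0 to 7 days. The SE of the difference in means is SD × √(2/n).

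| Entry days | SD | n per arm | SE (days) | 95% range | Gap of 1 day or more |
|---|---|---|---|---|---|
| Continuous | 2.02 | 30 | 0.52 | ±1.02 | 5.5% |
| Continuous | 2.02 | 37 | 0.47 | ±0.92 | 3.3% |
| Whole days | 2.29 | 30 | 0.59 | ±1.16 | 9.1% |
| Whole days | 2.29 | 37 | 0.53 | ±1.04 | 6.0% |

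**4. Error rates with no drug effect.** 20,000 simulated trials per setting, whole-day entry, stage explaining an assumed 10% to 50% of day-5 variance, between-arm t test against a model adjusted for symptom days.
- Over all trials: unadjusted 4.8% to 5.2%, adjusted 4.7% to 5.2%. Neither is inflated.
- Only in trials with a gap of 1 day or more: unadjusted about 8% to 10% (10% explained), 18% to 21% (30%) and 25% to 28% (50%); adjusted about 4% to 6% throughout.

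These runs contain no day-0 viral load. Once that is in the model, only the remaining contribution of stage counts, so the lower settings are the closer guide.

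**5. Gain beyond day-0 viral load.** Assumed piecewise-linear log10 curves: decline 0.25 to 0.5 log10 per day, peak-time SD 1 to 3 days, swab noise SD 0.5 to 1.0 log10. Adding days since onset to a model with the day-0 value removes 7.0% to 18.4% of residual variance.
- Equivalent patients: 1/(1 − 0.070) = 1.08 and 1/(1 − 0.184) = 1.23, or 8% to 23% more.
- Power, starting from 80%: Φ(2.80/√0.930 − 1.96) = 83% and Φ(2.80/√0.816 − 1.96) = 87%.

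The result depends on where the peak is placed. With a rise of 1 log10 per day and the mean peak at symptom day 0, 1 or 3, the reduction runs over 4% to 14%, 8% to 24% and 9% to 52%. It is positive in every setting, but its size is not settled.

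**6. The two duration rules side by side.** Inclusion item 4, with a test pending, requires cough of more than 10 days. Exclusion item 2 removes anyone with acute respiratory symptoms beyond seven days. The protocol's own disease classification lists cough among such symptoms, so a patient entering by the first rule is removed by the second. The 0-to-7-day range used in step 3 is therefore itself an assumption.

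**The case against.** The choice of covariates is commonly left to a statistical analysis plan, which is not shown here, and the Data Analysis sentence allows other tests. A reader might infer that the trial ignores infection stage. The text does not support that: it names no adjustment, but does not rule one out. What remains is that the one method it does name cannot compare arms or hold a covariate. Nor can a later plan recover a day count that was never written down: applying exclusion 2 needs only a yes or no at seven days, and the Study Assessment Table has no explicit item for onset.

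A reader might also infer that a chance imbalance in stage would pass as a drug effect. Randomisation answers this. Such imbalance is already part of the standard error of an unadjusted between-arm comparison, and overall error stays near 5%. Only the error conditional on an observed gap rises, and gaps of a day or more are uncommon under the assumed entry pattern.

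It is fair, too, that every size given rests on assumed curves, and that a comparison with a plain change score would look larger only because it credits symptom days with the gain from day-0 adjustment. Finally, the trial calls itself exploratory. That lowers the stakes, but the change is still worth its small cost.

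**Conclusion.** The point holds as a cheap improvement to the analysis, not as a claim of bias. The named paired t test does not answer the randomised question and uses no prognostic baseline information. A between-arm model with day-0 viral load and days since onset would do both. The increment from days since onset is roughly 7% to 18% of residual variance, which would lift an 80%-power comparison to about 83% to 87%. This rests wholly on assumed viral curves and a uniform 0-to-7-day entry pattern, and other placements of the peak widen the range. The protocol gives no viral-load SD, slope or entry distribution with which to narrow it. The contradiction between the two symptom-duration rules stands independently of any of these assumptions.

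**What to change.** - Record the number of days since symptom onset at screening, where exclusion 2 already requires duration to be asked, and show it by arm at baseline.
- State that the primary viral-load comparison is between arms, on day-5 log10 viral load, in a linear model with arm, day-0 log10 viral load and days since onset as pre-specified covariates. Make clear in Study Design, as the Study Assessment Table does, that the day-0 RT-PCR is quantitative.
- Pre-specify the handling of patients without symptoms, for example days since first positive test with an indicator term. This is an imperfect substitute, because test date depends partly on access to testing.
- Reconcile the cough rule in inclusion item 4 with exclusion item 2.

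The analysis change costs one CRF field, a sentence or two of protocol text, and two degrees of freedom (three with the indicator) out of about 60. Sample size and treatment are unaffected.
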